## Abstract

**Background:**

Electroencephalographic (EEG) status epilepticus is described in 10 to 35% of patients with postanoxic encephalopathy after successful cardiopulmonary resuscitation and is associated with case fatality rates of 90 to 100%. It is unclear whether these EEG patterns represent a condition to be treated with anticonvulsants to improve outcome, or an expression of severe ischemic damage, in which treatment is futile.

**Methods/Design:**

TELSTAR is a multicenter clinical trial with two parallel groups, randomized treatment allocation, open label treatment, and blinded endpoint evaluation (PROBE design). We aim to enroll 172 adult patients with postanoxic encephalopathy and electroencephalographic status epilepticus after successful cardiopulmonary resuscitation, admitted to the ICU, in whom continuous EEG monitoring is started within 24 hours after admission. Patients are randomly assigned to either medical treatment to suppress all electrographic seizure activity, or no treatment of electroencephalographic status epilepticus. Antiepileptic treatment is based on guidelines for treatment of overt status epilepticus and is started within 3 hours after the diagnosis. If status epilepticus returns during tapering of sedative medication after suppression of all epileptiform activity for 2 × 24 hours, it will be considered refractory. The primary outcome measure is neurological outcome defined as the Cerebral Performance Category (CPC) score at 3 months, dichotomized into ‘good’ (CPC 1 to 2 = no or moderate neurological disability) and ‘poor’ (CPC 3 to 5 = severe disability, coma, or death). Secondary outcome measures include mortality and, for patients surviving up to 12 months, cognitive functioning, health related quality of life, and depression.

**Trial registration:**

Clinicaltrials.gov; NCT02056236. Date of registration: 4 February 2014.

## Background

After successful cardiopulmonary resuscitation, 64 to 74% of patients remain unconscious at hospital arrival as a result of diffuse postanoxic encephalopathy [1, 2]. In these patients, a spectrum of electroencephalographic (EEG) changes can be observed, reflecting varying extents of ischemic brain injury [3]. Electroencephalographic status epilepticus is described in 10 to 35% [3–8] and is strongly associated with poor outcome: case fatality was 90 to 100% in prospective case series, despite treatment with anticonvulsants [4, 6–10]. Without EEG monitoring, approximately one in five cases remains undiscovered due to the absence of clinical signs [6, 11, 12].

The diagnostic criteria for electroencephalographic status epilepticus in comatose patients with postanoxic encephalopathy are controversial [13, 14]. The American Clinical Neurophysiology Society defines unequivocal seizures as generalized spike-wave discharges at 3 Hz or faster or clearly evolving discharges of any type at 4 Hz or faster, either focal or generalized [15]. However, some experts also consider other rhythmic or periodic patterns, such as generalized or lateralized periodic discharges or rhythmic delta activity as seizure activity [6, 8].

It is unclear whether electroencephalographic seizure patterns in patients with postanoxic encephalopathy represent a condition which can be treated with anticonvulsants to improve patients’ outcome, or have to be regarded as an expression of severe ischemic damage, in which treatment with anticonvulsants would be futile [16, 17]. Case series suggest that in patients with electroencephalographic status epilepticus, preserved brainstem reactions and EEG background reactivity are associated with a favorable outcome [4]. It is unclear whether treatment with anticonvulsants reduces the risk of a poor outcome in these patients and if so, how intensive this treatment should be. In the only prospective, non-randomized intervention study, a stepwise treatment up to pentobarbital-induced burst suppression resulted in a good outcome for 6% of patients with clinically overt or electroencephalographic status epilepticus [18]. This proportion is approximately the same as reported in observational studies, irrespective of treatment [4, 6, 8, 9].

Despite the lack of evidence, most neurologists treat status epilepticus in comatose patients after cardiopulmonary resuscitation with anticonvulsants. Increased detection of electroencephalographic status epilepticus by continuous EEG monitoring has led to increased prescription of these drugs [19, 20]. However, treatment is mostly moderately intensive. In The Netherlands, only one third of physicians treat these patients equally intensively as those with clinically overt status epilepticus [21]. Both intensive antiepileptic treatment and no treatment of electroencephalographic status epilepticus are considered standard modalities, where some experts believe that treatment is useless and others that it is unethical to withhold it.

Apart from the intensity, the timing of treatment is probably an important determinant of treatment effect. Mechanisms such as excessive glutamate release are known to worsen brain damage in ongoing status epilepticus within 20 to 40 minutes, even without clinical signs and despite good oxygenation [22]. Also, prolonged duration of status epilepticus reduces the effect of treatment; for example, due to receptor trafficking [23]. In approximately a quarter of patients, the electroencephalographic status epilepticus starts within 24 hours after cardiopulmonary resuscitation [5, 10, 12]. In previous studies, EEG monitoring started at a median of 2 to 3 days after cardiopulmonary resuscitation, indicating that diagnosis and subsequent treatment of electroencephalographic status epilepticus started relatively late [4, 8].

We conclude that evidence for a beneficial effect of medical treatment of electroencephalographic status epilepticus in patients with postanoxic encephalopathy after cardiopulmonary resuscitation is insufficient. To be effective, treatment should be sufficiently intensive and initiated as early as possible after the onset of status epilepticus. Therefore, we aim to study the effect of intensive and early medical treatment of electroencephalographic status epilepticus on functional outcome of comatose patients after cardiopulmonary resuscitation in a randomized controlled clinical trial.

### Hypothesis

Medical treatment of electroencephalographic status epilepticus improves outcome of patients with postanoxic encephalopathy after successful cardiopulmonary resuscitation.

## Methods/Design

### Design and population

TELSTAR is a multicenter clinical trial with two parallel groups, randomized treatment allocation, open label treatment and blinded endpoint evaluation (PROBE design). The trial has been registered in the United States National Institutes of Health Clinical Trials registry (clinicaltrials.gov, identifier NCT02056236) on 4 February 2014. The study population consists of comatose adult patients after cardiopulmonary resuscitation, admitted to the ICU, with electroencephalographic status epilepticus on continuous EEG. Detailed eligibility criteria are listed in Table 1.

**Table 1 Tab1:** **Eligibility criteria**

Inclusion criteria	Exclusion criteria
Patients after successful cardiopulmonary resuscitation with suspected postanoxic encephalopathy	A known history of another medical condition with limited life expectancy (<6 months)
Age 18 years or older	Any progressive brain illness, such as a brain tumor or neurodegenerative disease
Continuous EEG with at least 8 electrodes started within 24 hours after cardiopulmonary resuscitation	Pre-admission glasgow outcome scale score of 3 or lower
Electroencephalographic status epilepticus on continuous EEG	Reason other than neurological condition to withdraw treatment
Informed consent given by a legal representative	Follow-up impossible due to logistic reasons, for example not living in The Netherlands
Possibility to start treatment within 3 hours after detection of electroencephalographic status epilepticus^a^	Known participation in any interventional study

^a^If status epilepticus is present at initiation of continuous EEG, the starting time of continuous EEG is considered as detection time. EEG = electroencephalography.

Definitions of electroencephalographic status epilepticus will be according to standardized critical care EEG terminology [15]. They may consist of generalized spike-wave discharges at 3 Hz or faster, clearly evolving discharges of any type at 4 Hz or faster (either generalized or focal), or periodic discharges (generalized or lateralized) at any frequency. For continuous seizure activity, the minimum duration requirement is 30 minutes. Intermittent seizures of 5 minutes and longer, recurring at least twice, with seizure-free intervals shorter than 60 minutes will also be included. EEG assessment for inclusion will ultimately be left to the discretion of the treating neurologist or clinical neurophysiologist.

### Informed consent

Written informed consent will be obtained from the patient's authorized representative prior to the performance of any protocol-specific procedure. Surviving patients will be asked for informed consent for participation and additional follow-up on long-term outcome. Separate informed consent will be asked for neuropsychological examination at 12 months, if applicable. The study will be conducted according to the principles of the Declaration of Helsinki (Seventh Revision, Fortaleza, 2013) and in accordance with the Dutch Medical Research Involving Human Subjects Act (WMO) and local guidelines.

### Treatment allocation

All participating subjects receive standard best medical management according to current guidelines, including therapeutic hypothermia or controlled normothermia with sedation for 24 hours. In addition, they will be randomly assigned to either medical treatment or no treatment of electroencephalographic status epilepticus. In both groups, decisions regarding limitation or withdrawal of treatment will be made in accordance with the Dutch guidelines for postanoxic coma management [24]. Reasons for withdrawal of treatment will be documented.

Subjects will be randomized using ALEA (Clinical Trial Center Maastricht, The Netherlands), which is an online, central randomization service. To prevent imbalance of allocated treatments, blocked randomization will be used, with a 1:1 allocation, stratified by center, and random block size ranging from 4 to 10 subjects.

### Intervention group: treatment of electroencephalographic status epilepticus

Since no treatment with anticonvulsants has been proven superior to another, the choice of medication is ultimately left to the discretion of the treating neurologist, based on local protocols. However, to prevent large differences with respect to the intensity of treatment, recommendations are made as displayed in Figure 1. In summary, treatment consists of a stepwise approach, from intermittent administration of antiepileptic drugs up to treatment with barbiturates, in accordance with international guidelines for treatment of overt status epilepticus [25, 26]. Each subsequent step is taken as soon as possible when previous steps fail to suppress epileptiform activity. The treatment objective is to suppress all epileptiform activity on the EEG during at least 24 hours. Induction of burst suppression is not obligate. If the status epilepticus returns after tapering sedative medication, the treatment procedure will be repeated during another 24 hours. If status epilepticus returns after 2 × 24 hours, it is considered refractory. We accept that treatment with barbiturates may lead to prolonged hospitalization of several days due to their influence on prognostic tests.

**Figure 1 Fig1:**
[figure not shown]
**Stepwise treatment approach for electroencephalographic status epilepticus.** Each consecutive treatment step is taken when previous steps have failed to suppress electroencephalographic seizure activity. After 24 hours of treatment, sedative agents (thiopental, propofol, and continuously administrated benzodiazepines) will be tapered and intermittently administrated antiepileptic drugs (phenytoin, valproic acid, and levetiracetam) will be continued. If the status epilepticus returns, the treatment procedure will be repeated during another 24 hours. If status epilepticus returns after 2 × 24 hours, it is considered refractory. EEG = Electroencephalography.

### Control group: no treatment of electroencephalographic status epilepticus

In this group, patients will be treated according to standard guidelines for treatment of comatose patients after cardiopulmonary resuscitation, without EEG-based treatment of status epilepticus. Treatment to suppress clinically manifest myoclonic jerks in this group, and in those patients surviving beyond ICU discharge, is left to the discretion of the treating physician.

### Outcome assessment

The primary outcome measure is neurological outcome, defined as the Cerebral Performance Category (CPC) score at 3 months, dichotomized into ‘good’ (CPC 1 to 2 = no or moderate neurological disability) and ‘poor’ (CPC 3 to 5 = severe disability, coma, or death).

Secondary outcome measures include mortality, CPC scores at 6 and 12 months, length of stay on the ICU, duration of mechanical ventilation, and seizure recurrence rate within 12 months. In case of survival, additional outcome measures include quality of life after a year as measured by the Medical Outcomes Study 36-item short-form health survey (SF-36) [27], depression after a year as measured by the Montgomery and Åsberg Depression Rating Scale (MADRS) [28], and cognitive functioning after a year as measured by detailed neuropsychological examination. Secondary outcome measures will not be collected to test between-group differences, since the estimated number of survivors is small. These measures will be collected to thoroughly assess outcome and quality of life of survivors.

Additionally, a limited amount of data on the use of resources will be collected for analysis of cost-effectiveness, including place of residence at one year and admission to hospitals, rehabilitation centers, and nursing homes within the first year.

### Study procedures and data collection

For data collection and management, the OpenClinica open source software (OpenClinica LLC and collaborators, Waltham, MA, USA) will be used. At randomization, patients receive a study number by which all data is coded. The trial coordinator and principal investigator safeguard the key to this code.

Figure 2 shows the study flow chart. In participating hospitals, continuous EEG monitoring is part of regular patient care and is initiated as soon as possible after admission to the ICU. In order to detect seizure activity early, continuous EEG registrations are checked three-hourly by a neurologist, clinical neurophysiologist, or clinical neurophysiology technician. For practical reasons, these checks will not take place regularly between midnight and 8 am. When patients meet the eligibility criteria and informed consent is obtained, they will be randomly allocated to one of the treatment arms. It is not possible to see the treatment allocation before the patient is randomized and registered in the study database. Neither is it possible to withdraw the patient from the database after treatment assignment. After randomization, treating physicians and patients (or their legal representatives) will be aware of the treatment assignment.

**Figure 2 Fig2:**
[figure not shown]
**Study flow chart.** CPC = Cerebral Performance Category; MADRS: Montgomery and Åsberg Depression Rating Scale; SF-36: Medical Outcomes Study 36-item short-form health survey.

Baseline data will be obtained at randomization and include patient characteristics (age, sex, medical history, use of anticonvulsants), pre-hospital factors (cause and location of cardiac arrest, initial cardiac rhythm, time to return of spontaneous circulation), clinical parameters (Glasgow Coma Scale score, brain stem reflexes), electroencephalographic features (seizure pattern, background reactivity), target temperature, and the Acute Physiology and Chronic Health Evaluation (APACHE) score. During admission on the ICU, daily neurological examinations will be performed as part of regular care. Selected medication for treatment of the status epilepticus will be recorded. At ICU discharge or in case of mortality, the duration of ventilation and duration of admission will be assessed.

Follow-up will be done by means of a telephone interview by a trained investigator or research nurse, who is blinded for the allocated treatment. At 3, 6, and 12 months, CPC scores will be assessed. Place of residence, duration of admission in hospitals, rehabilitations centers, or nursing homes, seizure recurrence rates, use of anticonvulsants, and serious adverse events will be recorded. At 12 months, after obtaining separate informed consent, quality of life, depression, and cognitive functioning will be assessed in the local hospital.

Subjects can leave the study at any time for any reason if they wish to do so without any consequences. Also, the investigator can decide to withdraw a subject from the study for urgent medical reasons. Subjects will be replaced after withdrawal for any reason. Every attempt will be made to complete the primary follow-up in patients who are withdrawn from treatment.

### Statistical considerations

The primary analysis will be a single comparison between the treatment groups with regard to the primary outcome measure at 3 months, according to the intention-to-treat principle. To assess the effect of treatment with anticonvulsants, the absolute risk reduction of poor outcome will be calculated, including the corresponding 95% confidence interval. Baseline characteristics, raw distributions of the CPC score, and scores of secondary outcome measures will first be presented in a descriptive way. For secondary outcome measures, between-group differences will be analyzed by means of independent samples *t*-tests, Mann–Whitney tests, or Fisher exact tests, where appropriate. If necessary, multivariate regression analysis will be used to adjust for imbalances in main prognostic variables between the intervention and control groups.

Power calculations are hampered by the absence of data from randomized trials. With a presumed reduction of poor outcome from 99% to 92%, alpha of 5%, power of 80%, and 1-tailed testing, 84 patients per treatment group are needed to detect superiority of treatment with anticonvulsants. An O’Brien Fleming interim analysis will be performed after a total of 86 enrollments. If the difference between the treatment groups at that time is significant at *P* <0.00557, the trial will be stopped because of ‘proof beyond reasonable doubt’ that treatment with anticonvulsants is superior to treatment without anticonvulsants. To compensate for this interim analysis, two additional patients per group will be included. This indicates an intended sample size of 172 subjects.

With an estimated incidence of electroencephalographic status epilepticus of 20% in comatose patients with postanoxic encephalopathy [3], 860 patients will have to be monitored with continuous EEG. With five Dutch hospitals participating at the submission of this manuscript, we estimate an enrollment period of four and a half years.

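### The protocol both disclaims and prescribes between-group tests of secondary outcomes; for scores that exist only in 12-month survivors, such tests would not compare randomised groups

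*Protocol article*

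**What the plan says.** Two sections of the protocol article deal with between-group comparison of secondary outcomes.

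- Outcome assessment: "Secondary outcome measures will not be collected to test between-group differences, since the estimated number of survivors is small". The next sentence gives the purpose: "These measures will be collected to thoroughly assess outcome and quality of life of survivors".
- Statistical considerations: after an initial descriptive presentation, "For secondary outcome measures, between-group differences will be analyzed by means of independent samples" *t*-tests, Mann–Whitney tests or Fisher exact tests, chosen as appropriate. No outcome is excluded.

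Three further places show what the second statement covers.

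- The abstract (Methods/Design) counts the survivor scores among the secondary outcomes: "Secondary outcome measures include mortality and, for patients surviving up to 12 months, cognitive functioning, health related quality of life, and depression". Outcome assessment makes them conditional: "In case of survival, additional outcome measures include quality of life after a year", followed by depression and cognition.
- The secondary list in Outcome assessment also contains "length of stay on the ICU, duration of mechanical ventilation". Study procedures and data collection says when these are recorded: "At ICU discharge or in case of mortality, the duration of ventilation and duration of admission will be assessed".
- The section on the intervention group accepts that "treatment with barbiturates may lead to prolonged hospitalization of several days due to their influence on prognostic tests".

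**The concern.** An analyst cannot follow both statements. If the choice is left open, it may be made in an open-label trial after results are known.

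For one group of outcomes the testing statement would also be the wrong one to follow. SF-36, MADRS and cognitive scores exist only in patients alive at 12 months. Survival is determined after randomisation, and the trial's hypothesis is that treatment changes outcome; Safety assessments adds that it may lower the risk of death. If it does, the survivors in the two arms are different kinds of patient. A simple two-sample test of their scores then mixes any effect on quality of life with the effect on who is alive to be measured. At stake are published secondary p-values that look like randomised comparisons and are not, based on a handful of patients.

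**Working it through.** **Comparing the statements.** Both sections use the same general term, secondary outcome measures. Three ways of removing the conflict can be tried.

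1. The as-appropriate qualifier in Statistical considerations: it governs which of the three tests is used, not whether to test.
2. The initial descriptive presentation: it comes first and the tests follow, so it does not replace them.
3. Reading the disclaimer as covering only SF-36, MADRS and cognition: the abstract calls exactly these secondary outcomes, and Statistical considerations tests secondary outcomes without exception. The conflict therefore remains for these scores.

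**How many survivors.** The protocol gives no expected number, so there is no figure to reproduce. Inputs: 172 patients, 86 per arm (Statistical considerations); case fatality 90 to 100% (Background). The assumption is that this fatality applies to this population at 12 months.

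- Survivors in total: 172 × (1 − 0.90) = 17.2; 172 × (1 − 1.00) = 0.
- Per arm: 86 × 0.10 = 8.6; 86 × 0 = 0.

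At a given fatality, the number with scores can only be lower, because the 12-month assessment needs separate consent.

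**How different the survivors could be.** The design assumes poor outcome in 99% of controls and 92% of treated patients.

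- Expected good outcomes, control: 86 × 0.01 = 0.86.
- Expected good outcomes, treated: 86 × 0.08 = 6.88.
- Share of the treated arm's good outcomes in excess of the control rate: (0.08 − 0.01) / 0.08 = 0.875.

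These are good outcomes, not all survivors, since CPC 3 and 4 also include living patients. Still, under the trial's own effect, about seven in eight treated patients with a good outcome have no counterpart in the control arm. Comparing scores among those alive would not compare like with like.

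**What a test could detect.** Power of a two-sided 5% *t*-test for assumed standardised differences:

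| Survivors per arm | 0.5 SD | 0.8 SD | 1.0 SD |
|---|---|---|---|
| 9 and 9 (upper end, equal split) | 17% | 36% | 51% |
| 4 and 7 (assumed) | 11% | 21% | 30% |
| 1 and 7 (design good-outcome counts, rounded) | 7% | 10% | 13% |

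For 80% power the difference must be about 1.41 SD with 9 per arm, or about 1.51 SD with 8 per arm. These figures support the protocol's own reason for not testing.

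**Durations.** ICU stay and ventilation time are recorded at ICU discharge or death, so death ends the clock. At 90 to 100% fatality many values may end that way, if many deaths occur in the ICU (an assumption). A shorter stay may then mean an earlier death, and a duration cannot be interpreted without vital status.

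**The case against.** The disclaimer can be read narrowly. It states why the measures are collected, and its reason, few survivors, fits SF-36, MADRS and cognition but not mortality, ICU stay or ventilation time, which exist for every patient. On that reading, testing mortality and CPC is unobjectionable. This stands, and it shapes the fix: the tests need limiting, not abolishing. It does not rescue the survivor-only scores, where the two sections still collide.

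Three stronger conclusions are tempting, and the document does not support them.

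- *That the plan rewards early death.* A reader might infer this from tests on raw durations. The protocol nowhere treats a shorter stay as a better result. It describes longer hospitalisation as something treatment may cause and that it accepts, and it collects resource-use data for cost-effectiveness. Raw duration is a legitimate measure of resource use, and the handling of death in duration endpoints is commonly left to an analysis plan, which is not shown here.
- *That uncorrected testing inflates false positives.* Nine secondary outcomes at 5% would give 1 − 0.95^9 = 37% if independent. They are not: mortality and the later CPC scores overlap heavily, and the three survivor scores share one small subset. Fisher's exact test is also conservative here, with an actual size of about 1.8% for 86 per arm and 5% survival in both. The protocol makes the primary analysis a single comparison and claims no confirmatory status for any secondary outcome.
- *That ICU-free and ventilator-free days are required.* With death scored zero, they would be zero in at least 90% of patients at the cited fatality. They would mostly restate mortality, and they need a time horizon that would have to be chosen.

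**Conclusion.** The point holds as a direct conflict between Outcome assessment and Statistical considerations, with a real consequence for the survivor-only scores. Following the testing sentence as written would compare SF-36, MADRS and cognition in 0 to about 17 patients selected after randomisation, and the result would not be a randomised treatment effect if treatment affects survival. The count rests on the cited 90 to 100% case fatality applying at 12 months; the power figures rest on assumed splits and effect sizes. The bias argument needs only that treatment may change who survives.

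For ICU stay and ventilation time the conclusion is weaker: they need vital status beside them and should not serve as tested evidence of benefit. The primary analysis, sample size and interim analysis are unaffected. The correction should be made, but it concerns secondary reporting only.

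**What to change.** Reconcile the two sections so that they state one rule.

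- In Statistical considerations, restrict the testing sentence to outcomes defined for all randomised patients: mortality, and CPC at 6 and 12 months with deaths included, as the CPC categories already do. Report these as supportive estimates with 95% confidence intervals.
- State that SF-36, MADRS and cognitive scores will be described by arm, each with the number of patients alive and the number assessed, without between-group tests.
- Present ICU stay and ventilation time by arm together with vital status, as resource use. Free-days endpoints are optional; if they are added, their time horizon must be stated.
- Align the sentence in Outcome assessment, so that it says which outcomes its disclaimer covers.

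This is a change of wording and needs no new data. What is given up is secondary p-values that Outcome assessment already says are not the purpose of collecting these measures.

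### The trial is sized for a one-tailed test at 5% but reports its primary result with a 95% CI, and the 80% power does not carry over to that interval

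*Protocol article*

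**What the plan says.** All the relevant text is in the protocol article under Statistical considerations.

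- **Sizing.** For a fall in poor outcome from 99% to 92%, the plan gives "alpha of 5%, power of 80%, and 1-tailed testing, 84 patients per treatment group are needed to detect superiority". It then adds patients for the interim look: "To compensate for this interim analysis, two additional patients per group will be included". "This indicates an intended sample size of 172 subjects", that is, 86 per group.
- **Primary analysis.** "The primary analysis will be a single comparison between the treatment groups with regard to the primary outcome measure at 3 months", by intention to treat. For the treatment effect, "the absolute risk reduction of poor outcome will be calculated, including the corresponding 95% confidence interval". The article names no test for this outcome.
- **Interim.** After 86 enrollments: "If the difference between the treatment groups at that time is significant at" P < 0.00557, the trial stops for superiority.
- **Named tests.** Fisher's exact test appears only in the list for secondary outcomes.

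**The concern.** A one-tailed test at 5% corresponds to a two-sided 90% interval, while a conventional 95% interval corresponds to 2.5% in each tail. The sizing sentence and the reported primary interval therefore set different bars. With a large expected difference and common events this would be a matter of presentation. Here the expected number of good outcomes is 86 × 0.01 = 0.86 in controls and 86 × 0.08 = 6.88 in the treated arm, so one or two patients can decide which bar is passed.

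The trial could thus end with a one-tailed test that declares superiority beside a 95% CI that includes zero, and with nothing in the article to say which carries the conclusion. A reader who takes the 80% to describe the reported interval would also be misled about how likely that interval is to be conclusive.

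**Working it through.** **Inputs** (Statistical considerations; the 1:1 ratio is under Treatment allocation): good outcome 1% in controls and 8% with treatment (the complements of 99% and 92%); alpha 5% one-tailed; 84 per group, raised to 86.

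**Method.** Exact power is the sum, over all pairs (x, y) of good outcomes, of Bin(x; n, 0.01) × Bin(y; n, 0.08) where the rule declares superiority. With p_C = x/n, p_T = y/n and d = p_T − p_C, the rules are:

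- Uncorrected z: d / √[2p(1−p)/n] > 1.645, where p is the pooled proportion.
- Wald 95% CI: d − 1.96 √[p_T(1−p_T)/n + p_C(1−p_C)/n] > 0.
- Newcombe 95% CI: d − √[(p_T − l_T)² + (u_C − p_C)²] > 0, where l_T and u_C are Wilson 95% limits.

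**Step 1: reproduce the plan's figure.** The uncorrected one-tailed z-test has exact power of 79.7% at 83 per group and 80.15% at 84. So 84 is the smallest size that reaches 80%. The usual closed formulas at one-tailed 5% do not give 84:

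- unpooled: (1.645 + 0.842)² × (0.01×0.99 + 0.08×0.92) / 0.07² = 105.4, so 106
- pooled: 108
- continuity-corrected: 135
- arcsine: 89

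**Step 2: power at 86 per group.**

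| Rule | Power |
|---|---|
| Uncorrected z, one-tailed 5% | 80.9% |
| Boschloo exact unconditional, one-tailed 5% | 70.9% |
| Wald 95% CI excludes zero | 65.2% |
| Uncorrected pooled z, two-sided 5% | 63.1% |
| Newcombe 95% CI excludes zero | 58.9% |

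These are fixed-sample figures. Taking the interim threshold as two-sided leaves the z and Wald rules at two-sided 5% at about 63-65%.

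**Step 3: how often the criteria disagree.** Every outcome for which either 95% CI excludes zero also passes the one-tailed z-test, so all disagreement runs one way. It is 80.9% − 65.2%, about 15.8% of trials (Wald), or 80.9% − 58.9%, about 22.1% (Newcombe).

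**Step 4: an example.** Take 3 good outcomes among 86 treated and 0 among 86 controls. The pooled proportion is 3/172 = 0.01744, so z = 0.03488 / √(2 × 0.01744 × 0.98256 / 86) = 1.747 and one-tailed p = 0.040. The Wald 95% lower limit is 0.03488 − 1.96 × √(0.03488 × 0.96512 / 86) = −0.0039. The Newcombe lower limit is also below zero. With no good outcomes in controls, the number needed in the treated arm is 3 (uncorrected one-tailed z), 4 (Wald 95% CI or Boschloo) or 5 (Newcombe 95% CI).

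**Step 5: does the uncorrected test hold 5%?** The same enumeration with one common good-outcome rate in both arms, at 86 per group, gives a one-sided size of 2.4% at a rate of 1%. The maximum is 6.2%, at about 3.3%.

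**Step 6: the interim threshold.** O'Brien-Fleming-type spending of a total 5% at half the information gives 2 − 2Φ(1.96/√0.5) = 0.00557, the plan's value. This fits a one-sided 5% design.

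**The case against.** The strongest reply is that the design is coherent as one-sided 5%. The sizing sentence says so openly, the interim threshold fits it, and 84 is right for it. On this view the 95% CI is only an estimate printed beside the test, which is common practice, and the exact test and interval method belong in a statistical analysis plan that is not shown. Much of this stands. A reader might infer that the primary analysis itself has only 59-65% power. The article does not support that, because it never says success is judged by the interval excluding zero; two-sided is also the conventional reading of a 95% CI, not a stated one. Nor is the absence of a named test a fault in a condensed article.

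Three other strong readings also fail. Fisher's test cannot be held against the primary analysis, since it is listed only for secondary outcomes. The uncorrected test cannot be said to break its level under the planning assumption: at a 1% good-outcome rate it is conservative, and the largest excess is 1.2 points. An exact unconditional test is one defensible choice, not something the plan must adopt.

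What the reply does not remove is the mismatch between two statements in the same section. The interval is introduced as the means of assessing the treatment effect, and it is stricter than the criterion that produced the sample size. If one-tailed 5% is meant throughout, the 95% CI is the element out of step.

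**Conclusion.** The concern holds as a mismatch, not as a calculation error. The 80% belongs to an uncorrected one-tailed 5% z-test and is not a property of the 95% CI reported for the primary outcome. If that interval had to exclude zero, power at 86 per group would be about 59% (Newcombe) to 65% (Wald), and it would disagree with the sizing criterion in about 16-22% of trials.

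This rests on the plan's rates of 99% and 92%, 86 evaluable patients per group, a two-sided reading of the 95% CI, and fixed-sample calculation.

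The level of the uncorrected test is a secondary point. A common good-outcome rate above the assumed 1% is plausible, since the article's Background reports 6% in the only prospective intervention study and about the same in observational series. A test that holds its level across that range is therefore worth naming.

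**What to change.** Keep 172 patients and state one final decision rule.

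- **If the one-sided test decides** (the reading that best fits the sizing and the interim): say so, and give the final level after adjustment for the interim look. Name a test that holds that level at low event rates. Report the matching two-sided 90% CI beside the 95% CI, and restate power for the named test. An exact unconditional (Boschloo) test is one option, with fixed-sample power of about 71%; the figure should be recomputed at the adjusted level.
- **If the 95% CI is to carry the conclusion:** say so, name the interval method, and restate power as about 59-65%.

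Either way the change is to wording only and needs no extra patients. The cost is a stated power below 80%.
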